### Intervention

The intervention group will be able to use a game-based appointment system in the web app, allowing them to book an appointment at the hospital venereology unit, in addition to all the educational content of sjekkdeg.no.

The control group will have access to the educative web app only.

### Outcomes

#### Primary outcome

The primary outcome is the number of consultations with health professionals. We expect the number of visits with health professionals will be higher in the game-based appointment group (Group B) when compared to the control group (Group A).

To assess if the game-based appointment system increases the number of consultations on STDs at the venereology unit at the University Hospital of North Norway, we will analyse the total number of appointments booked through the web app within one year after implementation and compare this data with earlier appointments rates. We will compare the total number of STDs consultations belonging to Group A versus the total number of consultations attended through the game-based appointment-system (Group B) within one year of implementation (quantitative approach). To compare the total number of STDs consultations, users in the control group are asked to bring their symptom checker results including their randomization code, to the visit at the venereology unit. Attended visits at the venereology unit of users showing randomization codes belonging to the control group will be registered in a grid.

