**Methods:**

The purpose of the study is to assess the impact of a game-based appointment system on the frequency of consultations at a venereology unit and on the use of an educational web app. An A/B testing methodology is used. Users from the city of Tromsø, in North Norway, will be randomized to one of the two versions of the game-style web app on sexual health at www.sjekkdeg.no. Group A will have access to educational content only, while group B will have, in addition, access to a game-based appointment system with automatic prioritization. After one year of the trial, it will be analyzed if the game-based appointment system increases the number of consultations at the venereology unit and if health professionals deem the system useful.

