The system was reviewed by a panel of specialists in venereal diseases. They contributed in the definition of the relevant symptoms that influence the priority attributed to the patients by the system. We envisaged three levels of prioritization (i.e. triage): 1) Emergency appointments: The user should see a doctor on the same day or the following day. Patients having fever or other signs of serious infection are assigned to this category. They are strongly advised to call the clinic by phone and should not use the game-based appointment system. 2) Haste-appointments: The user should see a doctor within 3-4 days. Typical cases are acute infections with itch or pain. 3) Routine-appointments: The user should see a doctor within 2-3 weeks. Most cases in this category are asymptomatic infections.

To book an online appointment the user will require a reference number that will appear jointly with the guided diagnosis provided in the symptom checker. Example of the user’s screen to book an appointment can be seen in Figure 1. This reference number will be the user’s “credentials” at the clinic. Simultaneously, the venereology unit will get an automatic notification with the provisional pre-selected day and time for the appointment, and the user’s symptoms report, which could be relevant for planning the workflow at the clinic. The appointment at the venereology unit is accepted by the health professionals once the user sends a SMS confirming his/her intention of showing up. Figure 2 shows the health professionals’ administration dashboard.

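### The plan asks whether the system raises the venereology unit's STD consultations, but neither planned comparison measures the unit's total

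*Protocol article*

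**What the plan says.** The protocol article frames its primary question at the level of the clinic. The Primary outcome section introduces the analysis with "To assess if the game-based appointment system increases the number of consultations on STDs at the venereology unit", and the Methods paragraph of the Abstract says that after one year "it will be analyzed if the game-based appointment system increases the number of consultations at the venereology unit".

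The Primary outcome section then names two comparisons:

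- **Before/after:** "we will analyse the total number of appointments booked through the web app within one year after implementation and compare this data with earlier appointments" (the comparator being past rates).
- **Between groups:** consultations belonging to Group A against consultations that Group B attended through the booking system, over the same year.

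Both groups are seen in one place. The Intervention section describes the Group B version as "allowing them to book an appointment at the hospital venereology unit, in addition to all the educational content of sjekkdeg.no". For Group A, "Attended visits at the venereology unit of users showing randomization codes belonging to the control group will be registered in a grid". Under Trial design, when a Group B user books, "the venereology unit will get an automatic notification with the provisional pre-selected day and time for the appointment". The same section sends emergency cases to the clinic by phone. It also makes an online appointment depend on the user's SMS confirmation, after which staff accept it.

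The article gives no number of places, no statement that places are full or fixed, and no all-route count of consultations during the trial year. Its limitations section deals only with generalizability.

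**The concern.** The question concerns a total: how many STD consultations the unit provides. The first comparison contrasts two sets of app users, and the second counts one booking route. Either could come out favourably while the unit's total stayed flat. A Group B user who books online might otherwise have phoned, and a place taken online might be one that a Group A user or another patient would have had.

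At stake is the wording of the conclusion. The Limitations section makes success a reason to extend the system to further venereology units. A clinic deciding on that needs to know whether more people will be seen, or whether the same number will arrive by a different door.

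**Working it through.** **1. The plan's own figures.** From Sample size: 1000 users, 50% attendance in Group A, a 20% change, alpha 0.05, and 0.80 (labelled beta, read here as power). From Randomisation: 1:1, so 500 per group. Assumptions: two-sided test, and the 20% read as relative.

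- 50% against 60%, 500 per group: power 0.89; 776 users in total would give 80%.
- 30% against 39% (the second scenario): power 0.85; 874 users would give 80%.

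The stated 0.80 is not reproduced exactly, but it errs on the safe side. The present point does not depend on it.

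**2. What each comparison measures.**

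| | Whose visits | Routes | Attended or booked |
|---|---|---|---|
| Stated question | all STD patients of the unit | all | consultations |
| A against B | app users in each group | for B, through the system | attended |
| Before/after, trial year | app users | web only | booked |

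Neither comparison matches the first row. The before/after comparison has a further difficulty. Trial design describes the booking system as new, so the earlier rates cannot be web-booking rates. A one-route count is being set against something else.

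**3. Shift between routes.** In the 50% scenario:

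- Group A: 500 x 0.50 = 250 visits.
- Group B: 500 x 0.60 = 300 visits.
- Difference: 300 - 250 = 50.

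If all Group B visits were booked online (an assumption), the app would log at least 300 bookings. By the Group A rate, 250 of those visits would have happened anyway. Even with no displacement, only 50 of the 300 are additional.

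**4. Displacement of patients outside the trial.** Let d be the share of the 50 extra Group B visits that replace visits by other patients. The documents do not give d, so the range 0 to 1 is assumed. Net change at the unit = 50 x (1 - d):

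- d = 0: +50
- d = 0.5: +25
- d = 1: 0

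The A-B difference is 50 throughout.

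**5. Displacement of Group A users.** Suppose Group B gains g visits, Group A loses s x g, and other patients lose (1 - s) x g. Net change at the unit is then 0 by construction, and the observed A-B difference is g x (1 + s). Setting that to 50:

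| s (assumed) | g | Group A | Group B | Other patients | Power to show B above A |
|---|---|---|---|---|---|
| 0 | 50 | 250 | 300 | -50 | 0.89 |
| 0.5 | 33 | 233 | 283 | -17 | 0.89 |
| 1 | 25 | 225 | 275 | 0 | 0.89 |

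At s = 1 each moved visit counts twice, so 25 moved visits show as 50. In the 30% scenario the difference is 195 - 150 = 45, and power is 0.85 to 0.88 over the same range of s. This shows what is possible. Zero net change was put in as a premise and is not a finding.

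**6. Could a higher yearly total serve as a condition on the claim?** The unit's volume is not given. Assume Poisson counts of 1,000, 3,000 or 10,000 a year. The SD of the difference between two years is the square root of twice the volume:

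| Volume a year (assumed) | SD of difference | Chance that a true gain of 50 shows no rise |
|---|---|---|
| 1,000 | 45 | 13% |
| 3,000 | 77 | 26% |
| 10,000 | 141 | 36% |

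A true change of zero would show a rise about half the time. This is before any time trend.

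**The case against.** The strongest reply is that displacement is nowhere documented. It needs places that are limited and taken, and the article says neither. The 2-3 weeks for routine cases is a triage target, not an observed queue. Fifty extra visits in a year is about one a week, which a clinic might absorb. The article also expects shorter consultations and less use of staff resources, which would ease capacity. An online slot is provisional until the user confirms by SMS, so an unconfirmed booking need not block anyone. All of this stands. A reader might infer that B above A would merely show who got the places, or that the A-B difference is inflated. The documents do not support either as a statement of fact.

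A second reply is that the trial also asks a per-user question. The Primary outcome section opens by expecting more visits in Group B than in Group A. The Background gives easier access to care for young people as the main aim. Trial design asks which version serves a typical user better, and Sample size works with an attendance rate per user. A against B addresses that question. This stands too, and it is why the remedy is largely one of wording.

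A third reply is that the before/after comparison already covers the unit, and that a condensed article may leave the definition of the earlier rates to the full protocol. This stands only in part. The definition of the earlier rates may be given elsewhere, but the article itself fixes the trial-year count as web bookings, and that is the wrong count for the question.

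**Conclusion.** The point holds as a mismatch between question and measurement. The Abstract and the Primary outcome section ask about the unit's consultations. One planned comparison is between app users, and the other counts bookings by one route. This is true even with no displacement at all, as step 3 shows.

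Displacement through the shared unit adds a possibility of unknown size. In the plan's 50% scenario, a difference of 50 visits between the groups is compatible with a net change at the unit anywhere from 0 to 50. That range rests wholly on the assumed d and may collapse to no problem. It also takes the 20% change as relative and 500 users per group.

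A reader might also infer that an increase should be claimed only if the unit's yearly total rises. Step 6 speaks against that: at the assumed volumes such a rule would often block a real gain and would pass a null one about half the time. An uncontrolled count should not overrule a randomised comparison.

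The change is worth making before the analysis. It does not touch the randomisation or the sample size.

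**What to change.** 1. State the A-B result as the effect on attendance per user offered online booking. Do not word A-B alone as an increase in the unit's total consultations, and align the Abstract and the Primary outcome section with this.
2. In the before/after comparison, replace web bookings with the unit's total attended STD consultations from all routes, by month, for 2015 and the preceding year.
3. Report the number of confirmed Group B bookings that were not attended.
4. Present the unit total descriptively, with its uncertainty and a note that it can move with time trends. Do not use it as a pass/fail condition on the randomised result.

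The cost is some rewording and a count from the unit's records, which the comparison with earlier rates is likely to need in any case. The price in interpretation is a narrower claim from the randomised comparison.

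### The primary A versus B comparison counts visits by two different rules: a shown code in Group A, a visit made through the booking system in Group B

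*Protocol article*

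**What the plan says.** The Primary outcome section opens with a general definition: "The primary outcome is the number of consultations with health professionals". It then fixes the randomised comparison as the "total number of STDs consultations belonging to Group A versus the total number of consultations attended through the game-based appointment-system (Group B").

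For Group A, "users in the control group are asked to bring their symptom checker results including their randomization code, to the visit at the venereology unit", and "Attended visits at the venereology unit of users showing randomization codes belonging to the control group will be registered in a grid". No other source for Group A visits is described.

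For Group B, the Trial design section describes the booking route. The user needs a reference number from the symptom checker: "This reference number will be the user’s “credentials” at the clinic". When the user books, "the venereology unit will get an automatic notification with the provisional pre-selected day and time for the appointment", and the appointment is "accepted by the health professionals once the user sends a SMS confirming his/her intention of showing up". The same section says of users triaged to the emergency category: "They are strongly advised to call the clinic by phone and should not use the game-based appointment system".

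Statistical methods describes attended visits that carry a randomization code and compares appointments attended by users in both groups. It does not limit Group B to booked visits and does not say how a code is collected from Group B. Randomisation states that neither users nor health professionals are blinded. Limitations and generalizability does not mention unequal recording of visits.

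**The concern.** Randomisation makes the two groups comparable, but the comparison stays fair only if an attended visit has the same chance of being counted in each. Here two features differ.

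- **Showing a code, with no back-up record, in A.** A Group A attender who forgets or does not offer the code leaves no trace in the trial data. A Group B attender who booked is expected by date, time, reference number and SMS.
- **Booking-route restriction in B.** A Group B user who attends after phoning, or by any other route, falls outside the stated count. A Group A user may come by any route and counts if the code is shown.

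The first feature inflates B relative to A; the second deflates it. A difference could be a recording artefact, and a null result could hide a real effect. The app is anonymous by design, so a missed visit cannot be traced to its arm afterwards. The rule has to be right before data collection.

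**Working it through.** **The two rules side by side**

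| | Group A | Group B |
|---|---|---|
| Symptom checker needed | yes (the code comes with its result) | yes (the reference number comes with it) |
| Identifier at the clinic | randomization code, if brought and shown | reference number |
| Record at the clinic before the visit | none described | booking notification and SMS confirmation |
| Booking routes that count | any | booking system only |

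**Inputs.** From Sample size: 1000 users (500 per arm at 1:1), Group A attendance of about 50% or 30%, effects of 20% and 30% (read as relative), alpha 0.05 (taken as two-sided), and a stated beta of 0.80 read as power. The protocol gives no capture rates, so these are assumptions: c is the share of Group A attenders who show a code, and s is the share of Group B attenders who come through the system and are recorded. As in Sample size, attendance is treated as a proportion of users.

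**Formulas.** Recorded rates are a = p_A × c and b = p_B × s, so

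recorded ratio = (p_B / p_A) × (s / c).

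The chance of a significant result, with m = (a + b)/2 and n = 500, is

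Φ{ [ |b − a| − 1.96 √(2m(1 − m)/n) ] / √([a(1 − a) + b(1 − b)]/n) }.

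**The plan's own figures first.** With c = s = 1, 50% versus 60% needs 388 per arm for 80% power, and 500 per arm gives 89%. For 30% versus 39% the need is 437 per arm, and 500 gives 85%. The planned 1000 is more than enough for the stated effects, so the sample size is not in dispute here.

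**No true effect.** Worked example with p = 0.30, c = 0.80, s = 1: a = 0.24, b = 0.30, m = 0.27. The standard errors are 0.0281 (null) and 0.0280. Then (0.06 − 1.96 × 0.0281)/0.0280 = 0.18, and Φ(0.18) = 0.57. The nominal chance of a significant result favouring B is 2.5%.

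| True attendance, both arms | c | s | Recorded A | Recorded B | Chance of a significant result |
|---|---|---|---|---|---|
| 30% | 0.90 | 1.00 | 27% | 30% | 18% |
| 50% | 0.90 | 1.00 | 45% | 50% | 35% |
| 30% | 0.80 | 1.00 | 24% | 30% | 57% |
| 50% | 0.80 | 1.00 | 40% | 50% | 89% |
| 30% | 0.80 | 0.90 | 24% | 27% | 19% |
| 50% | 0.80 | 0.90 | 40% | 45% | 36% |
| 10% (assumed) | 0.80 | 1.00 | 8% | 10% | 20% |

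With full capture in B, the plan's target ratios of 1.2 and 1.3 appear with no true effect once c falls to 1/1.2 = 0.83 or 1/1.3 = 0.77.

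**True effect, visits lost in B (c = 1).** For 30% versus 39%, the recorded rates are equal when s = 0.30/0.39 = 0.77, a loss of 23%. For 50% versus 60%, this happens at s = 0.50/0.60 = 0.83, a loss of 17%. With s = 0.90, power falls from 85% to 41% (30% versus 35.1%) and from 89% to 24% (50% versus 54%).

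**Equal capture.** If c = s, the recorded ratio equals the true ratio. The cost is power: with c = s = 0.80, 24% versus 31.2% and 40% versus 48% each give 72%.

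**The case against.** Several points on the other side are sound and limit what can be said.

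- A reader might infer that only Group A faces the symptom-checker hurdle. That is not so: the Group B reference number also comes from it.
- A reader might infer that Group B attendance is recorded automatically. The protocol says this only of the booking notification. How attendance is confirmed is not spelled out, and Group B users present an identifier too. What remains is that B has a back-up record and A has none.
- A reader might infer that a Group A user who phones would simply be counted. That user counts only if the code is shown.
- Statistical methods can be read as one code-based count for both arms. It supplies no procedure for collecting a code from Group B and does not override the booking-route wording in the Primary outcome section. The two sections conflict, and the reading does not settle which governs.
- The article condenses a fuller protocol, and the study flowchart is not shown, so Group B attendance logging may be set out elsewhere. That could answer how B attendance is logged. It would not remove the restriction to booked visits in the stated comparison.

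**Conclusion.** The concern holds for the A versus B comparison of the primary outcome: the protocol states a different counting rule for each arm, and following it as written can give a biased result.

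The net direction is unknown. It is tempting to conclude that the design favours Group B, or to quote 57% and 89% as the trial's false-positive risk. The documents support neither. Those two figures assume full capture in B, whereas the booking-route restriction means that B also loses visits. At 80% against 90% capture they fall to 19% and 36%, and they are smaller again if attendance is well below the planned 30% to 50%. All capture rates are assumptions. What the figures do show is that modest differences in capture are enough to create or erase an effect of the size the trial was planned to detect.

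**What to change.** Reconcile the Primary outcome and Statistical methods sections to one rule:

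1. Give every randomised Tromsø user a randomization code, with the same wording in both arms about bringing it to the unit.
2. Ask every STD attender at the unit for a sjekkdeg.no code, whatever the booking route, and enter it in the existing grid.
3. Define the primary outcome as any attended STD consultation by a randomised user with a shown code, by any booking route. Do not use the booking dashboard to add Group B visits to this count.
4. Report visits made through the booking system as a process measure in Group B only.
5. Keep self-report of the app version out of the primary count. Non-Tromsø users receive the same no-booking version without being randomised, so their answers would swell Group A, and recall cannot be assumed equal in unblinded arms. Use it at most in a sensitivity analysis, limited to attenders who say they answered that they were from Tromsø.

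None of this touches the triage advice.

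The cost is one reception question, a change to the app text and a rewritten outcome definition. The question also reaches attenders outside the consent steps described, which should be cleared beforehand. Visits without a shown code are lost in both arms, which lowers power (to 72% if 20% are lost in each). Group B users who book may still be likelier to have a code at hand, so some imbalance can remain.

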## Methods/Design

### Trial design

To assess the impact of the game-based appointment system, an A/B testing methodology is used. Two versions of the web app, www.sjekkdeg.no, will be used for the A/B test to explore the user interactivity with the site. Version A (control), consisting of the educative web app only; and Version B, which will additionally include a game-based appointment system. Users will be randomly selected to use one of the two versions of the web app. Thus, we will be able to assess which version better supports the typical user in tasks such as booking an appointment at the hospital venereology unit.

The novel game-based appointment system is integrated in the already existing web app www.sjekkdeg.no [10], a game-style web app on sexual health education including social media, targeting North-Norwegian youth, accessible through laptops, smartphones and tablet computers [10]. Gamification techniques [19] such as avatars, achievement-based gifts and social network sharing buttons have been implemented in www.sjekkdeg.no. The web app, which was launched at the end of 2012, seems to be a promising way to encourage users to learn more about sexual health, judging from preliminary visitor returning rates, the average pages visited and the time spent on it [19]. The data also show that the symptom checker is one of the most visited components of the web app [19].

The new game-based appointment system, made available to the users that have been randomized to the intervention group, is based on an automatic prioritization algorithm, which provides the opportunity to book an appointment online. Once randomized to the intervention group, a virtual doctor will ask questions concerning the symptoms that the avatar has experienced. According to the avatar’s answers, the virtual doctor suggests a possible diagnosis or, if a diagnosis is not possible, that the avatar should attend the clinic to be tested for STDs. The appointment system service will be available 24/7, from 1^st^ January 2015 until 31^st^ December 2015.

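### The primary outcome is handled differently by arm: only control users are asked to bring a code to the unit, and the two arms' visits are counted by different routes, so the net bias has unknown direction

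*Protocol article*

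**What the plan says.** The protocol article describes the control in two places. The abstract (Methods) says "Group A will have access to educational content only", and the Intervention section says "The control group will have access to the educative web app only".

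The Primary outcome section then adds a procedure for that arm. So that consultation totals can be compared, "users in the control group are asked to bring their symptom checker results including their randomization code, to the visit at the venereology unit". It continues: "Attended visits at the venereology unit of users showing randomization codes belonging to the control group will be registered in a grid". No other way of recording a Group A visit is described.

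For the other arm, the same section counts "the total number of consultations attended through the game-based appointment-system (Group B) within one year of implementation". Under Trial design, a Group B user needs a reference number to book, and the unit is notified automatically of the provisional appointment. Of that number the text says "This reference number will be the user’s “credentials” at the clinic".

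The Randomisation section states that neither users nor health professionals are blinded.

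**The concern.** Two things differ between the arms apart from the intervention, and both bear on the primary outcome.

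First, a request that exists only because of the trial is made to control users alone. It names the unit, refers to a visit there and gives the user something to present. If it nudges some users to attend, the comparator is no longer the educational app by itself. Better recording would not remove that effect, because it changes behaviour and not the count.

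Second, the counting rules differ. A Group A visit depends on the attender remembering, keeping and showing a code. A Group B visit is picked up by the booking system, but under the wording of the outcome only if it was booked there.

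With several arm-specific distortions of unknown size, some pulling up and some down, neither a positive nor a null result could be read with confidence as the effect of the booking system.

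**Working it through.** **The plan's own figure.** Inputs from Sample size: 1000 users at 1:1, taken as 500 per arm; control attendance about 50% with a 20% change, or 30% with a 30% difference; alpha 0.05. I read the printed beta of 0.80 as power, the changes as relative (50% to 60%, 30% to 39%) and the test as two-sided; the article does not state these.

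Power of the two-proportion z test is Φ(z), with z = [Δ√n − 1.96√(2p̄(1−p̄))] / √[pA(1−pA) + pB(1−pB)], where Δ = pB − pA and p̄ is their mean.

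- 50% v 60%: z = (0.10 × 22.361 − 1.96 × 0.7036) / 0.7000 = 1.224, power 0.89. For 80% power, 388 per arm are needed.
- 30% v 39%: z = (0.09 × 22.361 − 1.96 × 0.6723) / 0.6693 = 1.038, power 0.85. For 80% power, 437 per arm are needed.

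So 1000 users are more than enough for the stated changes. The sample size is not at issue; it only supplies the scenarios.

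**A cue alone.** Let d be the rise in Group A attendance caused by the request. The documents give no value; 1, 2.5 and 5 points are assumptions. With every visit captured:

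| d (points) | 50% v 60%: power | 30% v 39%: power |
|---|---|---|
| 0 | 0.89 | 0.85 |
| 1 | 0.82 | 0.76 |
| 2.5 | 0.67 | 0.57 |
| 5 | 0.36 | 0.26 |

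**A cue and missed codes together.** Let s be the share of control visits at which the code is shown, also an assumption. Observed difference = pB − (pA + d) × s, in percentage points:

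| Scenario | d | s = 1 | s = 0.95 | s = 0.90 | s = 0.80 |
|---|---|---|---|---|---|
| 50 v 60 (planned 10) | 0 | 10 | 12.5 | 15 | 20 |
| | 2.5 | 7.5 | 10.1 | 12.8 | 18 |
| | 5 | 5 | 7.8 | 10.5 | 16 |
| 30 v 39 (planned 9) | 0 | 9 | 10.5 | 12 | 15 |
| | 2.5 | 6.5 | 8.1 | 9.8 | 13 |
| | 5 | 4 | 5.8 | 7.5 | 11 |

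**Break-even.** The two distortions cancel when s = pA / (pA + d).

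- 50% scenario: 0.50/0.51 = 0.98, 0.50/0.525 = 0.95, 0.50/0.55 = 0.91. Missing about 2%, 5% or 9% of control visits undoes a cue of 1, 2.5 or 5 points.
- 30% scenario: 0.30/0.31 = 0.97, 0.30/0.325 = 0.92, 0.30/0.35 = 0.86, that is about 3%, 8% or 14%.

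If more than that is missed, the net distortion from these two sources is away from zero.

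**No true effect (both arms 50%).** With d = 0 and s = 0.90, the observed difference is 50 − 45 = +5 points. With d = 5 and s = 1, it is 50 − 55 = −5 points. With d = 5 and s = 0.80, it is 50 − 44 = +6 points. The sign depends entirely on the unknown inputs.

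**Group B visits outside the booking system.** These pull the other way again. If, as an assumption, 10% of Group B visits were arranged otherwise, the counted rate would be 0.60 × 0.90 = 54%, and the planned 10 points would become 4 with d = 0 and s = 1.

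**The case against.** A reader might infer that the request is itself a prompt to attend, so that the trial is biased towards no difference. The documents do not support that.

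- The text says what to bring to a visit, for counting purposes. It does not say that the request encourages attendance, nor when, where or how it is delivered. A cue effect is inference, and its size is assumed.
- The request concerns symptom-checker results, so it matters only to users of that component. A rise of 5 points across the whole arm would need a larger effect among them.
- The same section makes control visits depend on a shown code, which pushes the difference upwards. The direction towards zero holds only if every visit is captured, and this plan does not ensure that.

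It can also be said that Group B is cued too. Its virtual doctor may suggest, "if a diagnosis is not possible, that the avatar should attend the clinic to be tested for STDs", and its users also hold a number to present. This is true, but Trial design describes both as part of the booking system, so their effect belongs to the intervention under test. They do not justify a measurement procedure applied only to the comparator. The symptom-checker advice described under Participants goes to both arms and does not create a difference.

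Finally, Statistical methods speaks of attended visits with a randomization code without limiting this to Group A, so a common code route may be intended. The Primary outcome section nevertheless describes two routes, and a code request to controls only. The two sections should be brought into line.

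**Conclusion.** The point holds as one of unequal handling and ascertainment of the primary outcome in an unblinded trial. A trial-only request is made to one arm and lies outside the control as defined. Control visits are registered on showing a code, while Group B visits are counted through the booking system.

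The net bias is unknown in direction and size. A cue would shrink B minus A, missed control codes would enlarge it, and uncounted Group B visits would shrink it. A cue of 2.5 points with full capture would take power from 0.89 to 0.67 (50% v 60%) or from 0.85 to 0.57 (30% v 39%), but failing to register about 5% or 8% of control visits would cancel that shrinkage. These figures rest on assumed cue effects and capture shares, 500 per arm, a two-sided test and relative changes. They show how sensitive the comparison is and do not estimate what will happen. A claim that the design favours a null result, or a positive one, would go beyond the documents.

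**What to change.** - Show every randomised user, in both arms, the same study code at the same place with the same neutrally worded text.
- Have reception ask every STD attender at check-in for a sjekkdeg.no code. If it was not kept, ask whether they used the app and whether it offered online booking. Users who say they are not from Tromsø also see the control version without being randomised, so this fallback should also establish how the location question was answered.
- Count all attended visits in both arms by this one route, however booked. Do not count Group B through the booking system for the primary outcome; booking-system counts can be reported separately. Align Primary outcome and Statistical methods accordingly.

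Simply deleting the request to controls would not be enough. Group B bookings would still reach the unit automatically, so the losses would fall mainly on Group A and inflate B minus A.

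The cost is a change to the code text shown to users and one check-in question. Some attenders will have no code or will recall their version wrongly, so the number of unclassified visits should be reported with the result.
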